### Interim analyses {21b}

A formal interim analysis for safety is planned when the 3-month follow-up data of the first 50 randomized patients are obtained. This analysis will be performed by the independent third party for safety and the trial coordinator. The following stop criteria have been predefined:
3 m-FFS of vsAR and its two-sided 95% CI are entirely beneath the 3 m-FFS of tAR – 10%.> 30% difference between vsAR and tAR in de novo postoperative worsening of erectile function, defined as a decrease of ≥ 5 points on the postoperative IIEF-5 questionnaire compared to the preoperative IIEF-5 questionnaire.

If one of the stop criteria is reached, the independent third party for safety will discuss this with the central PI and the central Ethical Committee, and a decision about prematurely stopping the trial will be formulated and communicated to all parties involved in the trial.

### Methods for additional analyses (e.g., subgroup analyses) {20b}

Interaction tests for FFS were considered for traumatic versus non-traumatic stricture etiology and for primary versus secondary procedures. However, the rule of thumb says that at least 10 failures are needed per degree of freedom included in the model. Allowing for a modification of the effect of procedure by stricture etiology for instance would imply adding 3 degrees of freedom to the model (technique, center, and stricture etiology). This would lead to overfitting, which means the obtained results might not be reproducible in other samples. We will refrain from generalizing our findings from these (over)complex models to the larger population of patients and stick to purely descriptive results when considering more than one explanatory covariate.

The PP analysis of de novo postoperative worsening of erectile function after vsAR and tAR will be performed as well (two-sided Fisher’s exact test at the 20% significance level) to explore the effect of full-thickness transection on postoperative erectile function.

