### Criteria for discontinuing or modifying allocated interventions {11b}

Conversion of vsAR to tAR for any reason is allowed upon the operating surgeon’s discretion. These patients will be considered part of the vsAR group in the intention-to-treat (ITT) analyses and will be considered part of the tAR group in the per-protocol (PP) analyses.

All shifts of technique towards augmented urethroplasty or any technique other than AR due to any circumstance will be logged, but these patients will be excluded (post-hoc) from further analysis within this trial.

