## Statistical methods

### Statistical methods for primary and secondary outcomes {20a}

ITT analyses will be used for all end-points.

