#### Analysis of the primary end-point

Kaplan-Meier curves for FFS will be plotted with the corresponding log-log 80% CIs for vsAR and tAR.

Non-inferiority of vsAR versus tAR in terms of FFS at 24 months will be concluded when the lower limit of the 80% CI for the difference in FFS probability at 24 months does not exceed − 10%. Note that this analysis does not take into account the nesting of patients within centers, which may affect the estimated standard errors.

To take into account the clustering of patients within centers, a marginal Cox proportional hazards model can be fitted (using the cluster function from the “survival” package in R software) which will give a robust estimation of the variance. The lower limit of the 80% CI for the hazard ratio can be transformed into a limit of survival difference at 24 months, assuming an exponential distribution of failure-free survival times [*S*(*t*) = exp.{−*λt*}].

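### Non-inferiority on 24-month FFS rests on ITT alone although vsAR may be converted to tAR at will, and the set labelled 'PP' is an as-treated grouping

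*Protocol article*

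**What the plan says.** All references are to the Protocol article.

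- **Analysis set.** Statistical methods {20a}: "ITT analyses will be used for all end-points".
- **Decision rule.** Under Analysis of the primary end-point, non-inferiority is concluded when the "lower limit of the 80% CI for the difference in FFS probability at 24 months does not exceed − 10" per cent. No second analysis set is named for this comparison.
- **Conversion.** Criteria for discontinuing or modifying allocated interventions {11b}: "Conversion of vsAR to tAR for any reason is allowed upon the operating surgeon’s discretion". Converted men stay in vsAR for ITT, but each "will be considered part of the tAR group in the per-protocol (PP) analyses".
- **The one PP analysis.** Methods for additional analyses {20b}: "The PP analysis of de novo postoperative worsening of erectile function after vsAR and tAR will be performed as well", with the stated aim "to explore the effect of full-thickness transection on postoperative erectile function". FFS is not included.
- **Shifts to a technique other than anastomotic repair.** Section {11b} says these "will be logged, but these patients will be excluded (post-hoc) from further analysis within this trial". The set called ITT is therefore already not every randomised man.

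**The concern.** Conversion is foreseen in one direction only: a man allocated to the new technique receives the comparator and is still counted as a result of the new technique. In a superiority trial such mixing is conservative. In a non-inferiority trial it pulls the arms together and makes the claim easier, provided the converted men fare about as well as men in the tAR arm. The primary conclusion then needs a check that dilution did not produce it, and none is planned.

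The second problem is one of definition. A per-protocol set keeps those who received what they were allocated. The rule in {11b} instead reassigns men to the operation they received, which is an as-treated comparison. It gives up the balance of randomisation, and whatever led the surgeon to convert can confound it. Under a per-protocol label, readers would take the erectile-function result for something it is not.

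The article fixes its analysis set, defines its PP rule and assigns that rule to one secondary end-point. These are stated choices rather than details left open for a later document.

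**Working it through.** **Inputs from the article.** Sample size {14}: FFS 95.4% (tAR) and 95.3% (vsAR), limit 10 points, one-sided alpha 0.10, power 0.80, 41 evaluable and 50 recruited per arm.

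**Assumptions.** The conversion share c of the vsAR arm and the FFS q of converted men, because the article gives neither.

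**1. The plan's own figure.** With unpooled variance,
n = (z₀.₉₀ + z₀.₈₀)² × [p₁(1−p₁) + p₂(1−p₂)] / (0.10 − 0.001)²
= (1.2816 + 0.8416)² × (0.0439 + 0.0448) / 0.0098 = 40.8, so 41 per arm, as stated. The stated 50 follows from 41 × 1.2 = 49.2.

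**2. Dilution under ITT.** Let the true technique deficit equal the limit: tAR 95.4%, vsAR 85.4%. If converted men have tAR-like FFS, then
ITT vsAR FFS = (1−c) × 85.4 + c × 95.4, and the expected difference is −10 × (1−c).

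The chance of a false non-inferiority claim by normal approximation is Φ{(0.10 − |difference|)/SE − 1.2816}. For c = 10%: SE = √(0.864×0.136/50 + 0.954×0.046/50) = 0.0568, and Φ(0.01/0.0568 − 1.2816) = Φ(−1.106) = 13.4%. The exact column sums binomial probabilities with an unpooled Wald 80% CI.

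| c | ITT vsAR FFS | Difference (points) | Normal approx., n = 50 | Exact, n = 50 | Exact, n = 41 |
|---|---|---|---|---|---|
| 0% | 85.4% | −10.0 | 10.0% | 10.8% | 11.9% |
| 5% | 85.9% | −9.5 | 11.6% | 12.5% | 13.6% |
| 10% | 86.4% | −9.0 | 13.4% | 14.4% | 15.4% |
| 20% | 87.4% | −8.0 | 17.8% | 18.8% | 19.7% |

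Put the other way, a true deficit of 10/(1−c) points appears as exactly 10: 11.1 points at c = 10% and 12.5 at c = 20%. These figures treat FFS as a simple proportion; without censoring before 24 months the Kaplan-Meier estimate is the same.

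**3. What leaving converted men out would do.** Suppose there is no technique effect, overall FFS is 95.4%, and the men who would be converted are harder cases with FFS q. The remaining vsAR men then have FFS e = (95.4 − c×q)/(1−c). At c = 10%:
- q = 85%: e = (95.4 − 8.5)/0.9 = 96.6%, so vsAR gains +1.2 points.
- q = 75%: e = (95.4 − 7.5)/0.9 = 97.7%, so vsAR gains +2.3 points.

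An adherent set therefore has a bias of its own.

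**4. Erectile function.** Assume worsening in 20% after tAR and 10% after vsAR. With c = 10%, ITT vsAR worsening is 0.9×10 + 0.1×20 = 11%, and the benefit shrinks from 10 to 9 points. Here dilution works against vsAR.

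**The case against.** A reader might infer that both the ITT and the PP analysis lean towards vsAR. The article does not support that. The two concern different end-points: no PP analysis of FFS is planned, so the regrouping in {11b} cannot touch the non-inferiority conclusion. The lean of an as-treated comparison also needs converted men to have a worse prognosis, and the article says nothing of their prognosis; with average prognosis there is no bias. For erectile function, ITT dilution runs against vsAR (step 4). That part of the objection stands.

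Dilution is not automatic either. If converted men did badly, for instance 80% FFS with the other vsAR men unchanged at 85.4%, ITT vsAR would be 0.9×85.4 + 0.1×80 = 84.9%, a difference of −10.5 points, and nothing would be masked.

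The size may be small. Participating surgeons must declare themselves capable of both techniques, so nothing shows that conversions will be common. At 10% the attenuation is 1 point, against a planned 80% CI half-width of 1.2816 × √(0.0887/50) = 5.4 points. This is a declared phase II trial at a relaxed alpha, its one PP analysis has an exploratory purpose, and reasons for non-adherence are logged ({20c}).

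These arguments limit the severity but do not supply the missing check. With outcome assessors and data analysts unblinded ({17a}), a supportive set chosen after results are seen would carry little weight.

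**Conclusion.** The concern holds in two parts.

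1. The FFS non-inferiority conclusion rests on ITT alone in a trial that permits discretionary conversion to the comparator, and no FFS analysis by adherence is planned. If converted men do about as well as tAR men, and 5% to 20% of the vsAR arm is converted (assumed), a true 10-point deficit passes as non-inferior in 12.5% to 19% of trials instead of about 11%. If conversions are rare, the effect is negligible.
2. The set called PP is as-treated and confounded by the reason for conversion. It is used only for erectile function, so it is a matter of labelling and interpretation and not a threat to the primary result.

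This should be fixed; it does not invalidate the design.

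**What to change.** - Pre-specify a supportive analysis of 24-month FFS in men who received their allocated technique. Judge the lower limit of its 80% CI against the same −10-point limit and report it beside ITT.
- Report the number of conversions and the reasons by arm.
- State that a non-inferiority claim will be read cautiously if the two analyses reach different conclusions against the limit.
- State that leaving converted men out can itself favour vsAR if they are harder cases (step 3), so this set supports ITT and does not replace it.
- Relabel the regrouping in {11b} and {20b} 'as treated, exploratory'.

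The cost is a little extra analysis, with no added patients or visits. The claim becomes slightly harder to make if conversions are common. At 10% conversions the adherent vsAR group would be 45 men, and the half-width would widen only from 5.4 to 1.2816 × √(0.0448/45 + 0.0439/50) = 5.5 points.

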### Methods in analysis to handle protocol non-adherence and any statistical methods to handle missing data {20c}

Participant retention, protocol adherence, and minimization of missing data will be promoted by scheduling every foreseen follow-up moment (10 days, 3 months, 12 months, and 24 months postoperatively) in advance, ideally at the moment of inclusion or at the moment of discharge from the hospital. If patients do not show up at the foreseen follow-up moment and do not reschedule, they will be invited for a new appointment by telephone or e-mail.

In case of drop-out, patients will be contacted by the local PI and the reason for drop-out will be logged qualitatively. In case of no further contact with the participant at hand, “unknown reason for drop-out” will be logged. These participants will be censored at the moment of latest follow-up.

In case of protocol non-adherence, the reason for this will be logged qualitatively by the local PI.

Missing or incorrect data will be detected by software programs and will be reported transparently in the publication of trial results.

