### Sample size {14}

Power analysis and sample size calculation for this non-inferiority trial were performed using an online software package:

Sealed Envelope Ltd. 2012. Power calculator for binary outcome non-inferiority trial. [Online] Available from: https://www.sealedenvelope.com/power/binary-noninferior/ [Accessed Mon Apr 162,018].

Different scenarios were simulated, of which the results are discussed below. In all scenarios, 10% was considered the non-inferiority limit, *d*, as mentioned above.

- Scenario 1: power 0.80; estimated success in control group (tAR): 95.4%; estimated success in experimental group (vsAR): 95.3%; for different one-sided alphas:

❖ Alpha 0.025: 72 patients per arm

❖ Alpha 0.05: 56 patients per arm

❖ Alpha 0.10: 41 patients per arm

- Scenario 2: power 0.80; estimated success in control group (tAR): 95.4%; estimated success in experimental group (vsAR): 95.4%; for different one-sided alphas:

❖ Alpha 0.025: 69 patients per arm

❖ Alpha 0.05: 55 patients per arm

❖ Alpha 0.10: 40 patients per arm

- Scenario 3: power 0.80; estimated success in control group (tAR): 97.4%; estimated success in experimental group (vsAR): 93%; for different one-sided alphas:

❖ Alpha 0.025: 227 patients per arm

❖ Alpha 0.05: 179 patients per arm

❖ Alpha 0.10: 131 patients per arm

The numbers that were put in the above simulations are based on an in-home analysis of patients who underwent anastomotic repair at Ghent University Hospital between 2000 and 2017. Herein the FFS at 24 months for vsAR and tAR were 95.3% (standard deviation (SD), 2.3%) and 95.4% (SD, 2.0%) respectively. These exact results are represented in scenario 1. Scenario 2 represents a situation in which the surgical outcome would be exactly the same for vsAR and tAR. Scenario 3 represents a less favorable situation in which vsAR has a 24 m-FFS of 93% (95.3% − SD) and tAR has a 24 m-FFS of 97.4 (95.4% + SD).

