In every scenario, the power was set at 0.80, according to the guidelines for designing a phase II trial [21]. The results for different alphas are displayed above. Usually, a non-inferiority trial demands a significance level, alpha, of 0.025 as these trials only look at one boundary of the classic two-sided 95% confidence interval (CI) [22]. However, these conditions often lead to (sometimes unreasonably) high sample size calculations requiring excessive financing and recruitment. As a solution, researchers often design a phase II trial that allows for more coincidence and thus a trial with a higher significance level, alpha. Rubinstein et al. reported alpha values of 0.10 and 0.20 to be allowed in a phase II trial [21]. Considering the fact that a non-inferiority trial relies on one-sided testing, we believe a one-sided significance level, alpha, of 0.10 is allowed and most feasible.

Considering all of the above, a scenario in which the power is set at 0.80, the one-sided significance level, alpha, is set at 0.10, the estimated success in control group is set at 95.4%, and the estimated success in experimental group is set at 95.3% was found most realistic and feasible. Considering this and accounting for a realistic drop-out of 20% (experience based), it was estimated that each arm has to consist of 50 patients, resulting in a total sample size of 100 patients.

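### Every drop-out is censored at his last visit whatever the reason for leaving, and with about 10 lost men against 2 expected failures per arm, two or three unseen vsAR failures could decide non-inferiority

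*Protocol article*

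**What the plan says.** Section {20c} of the protocol article covers non-adherence and missing data. When a man drops out, "patients will be contacted by the local PI and the reason for drop-out will be logged qualitatively"; if he cannot be reached, the reason is recorded as unknown. The analytic rule follows: "These participants will be censored at the moment of latest follow-up". The reason has no stated role in the analysis.

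Under Analysis of the primary end-point, FFS is estimated by Kaplan-Meier. Non-inferiority is judged by whether "the lower limit of the 80% CI for the difference in FFS probability at 24 months" stays above -10%. Outcomes {12} defines failure by passage of a 16-Fr flexible cystoscope, and {18a} has this checked at 3, 12 and 24 months.

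Sample size {14} arrives at 50 men per arm after "accounting for a realistic drop-out of 20% (experience based". The assumed 24-month FFS is 95.3% for vsAR and 95.4% for tAR.

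**The concern.** Censoring in a Kaplan-Meier analysis gives a lost man the same future failure risk as the men still under observation in his arm. Failure can be seen only by cystoscopy at a trial visit. A man whose stricture recurs between visits and who is treated elsewhere therefore enters the analysis as failure-free up to his last visit and as a random loss afterwards. The rule treats him this way even if he tells the local PI why he left.

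In a non-inferiority trial, failures missed in the new arm favour the claim being tested. The expected events are few, and the men expected to be lost outnumber them about five to one. The primary conclusion may then depend on a handful of outcomes that nobody saw.

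**Working it through.** **Inputs from the article.** Margin: "10% was considered the non-inferiority limit" ({14}). Significance level: one-sided 0.10 ({14}), so z = 1.2816 for the two-sided 80% interval. Power: 0.80 ({14}). FFS: 95.3% and 95.4% ({14}). Drop-out: 20% ({14}).

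**The plan's own figure.** With unpooled variance, n = (1.2816 + 0.8416)² × (0.954×0.046 + 0.953×0.047) / (0.10 - 0.001)² = 40.8, so 41 per arm, as stated. Then 41 × 1.2 = 49.2, so 50 per arm, as stated. A 20% loss from 50 leaves 40 men observed and 10 lost per arm.

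**Expected failures among those observed.** 40 × 0.047 = 1.9 (vsAR) and 40 × 0.046 = 1.8 (tAR), so about 2 per arm. The ratio of lost men to expected failures is 10 to 2.

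**Formulas.** Let p1 be the vsAR and p0 the tAR failure-free proportion, and d = p1 - p0.
- Wald lower limit: d - 1.2816 × √[p1(1-p1)/n1 + p0(1-p0)/n0].
- Newcombe lower limit: d - √[(p1-l1)² + (u0-p0)²], where l1 and u0 are the 80% Wilson limits.

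**As planned, 38/40 v 38/40.** d = 0. Wald: 0 - 1.2816 × √(2 × 0.95×0.05/40) = 0 - 1.2816 × 0.0487 = -6.2%. Newcombe: the Wilson limits for 38/40 are 88.5% and 97.9%, so 0 - √(0.0645² + 0.0290²) = -7.1%. Kaplan-Meier with the 10 losses per arm placed at different visits gives -5.7% to -6.25%. Non-inferiority is concluded.

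**All 50 men per arm counted, with hidden failures added among the 10 lost vsAR men:**

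| Lost tAR men | Hidden vsAR failures | vsAR v tAR | d | Wald | Newcombe |
|---|---|---|---|---|---|
| none fail | 1 | 47/50 v 48/50 | -2.0% | -7.6% | -8.3% |
| none fail | 2 | 46/50 v 48/50 | -4.0% | -10.1% | -10.8% |
| none fail | 3 | 45/50 v 48/50 | -6.0% | -12.5% | -13.2% |
| observed 5% | 2 | 46/50 v 47.5/50 | -3.0% | -9.3% | -9.9% |
| observed 5% | 3 | 45/50 v 47.5/50 | -5.0% | -11.7% | -12.3% |
| one fails | 2 | 46/50 v 47/50 | -2.0% | -8.5% | -9.1% |
| one fails | 3 | 45/50 v 47/50 | -4.0% | -10.9% | -11.4% |

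The 47.5 is an expected value: 5% of 10 lost men is 0.5 failure. Example for 46/50 v 47.5/50: -0.03 - 1.2816 × √(0.92×0.08/50 + 0.95×0.05/50) = -0.03 - 1.2816 × 0.0492 = -9.3%.

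**Other lost men left censored.** If two hidden vsAR failures become known and all other lost men in both arms stay censored, the Kaplan-Meier limit is -10.9% to -11.8%. With one hidden failure it is -8.5% to -9.2%. The two-failure result is harsher than the full count because the other eight lost vsAR men then carry the raised vsAR failure risk.

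**How likely two hidden failures are.** The failure rate among lost men is not in the article. The binomial chance of two or more failures among 10 is about 8% at the planned 4.7%, 26% at an assumed 10%, and 62% at an assumed 20%.

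**The case against.** Censoring at last follow-up is the usual companion of a Kaplan-Meier analysis and contradicts nothing in the article. Participants are blinded ({17a}) and follow-up is the same in both arms, which argues against men leaving for reasons specific to one arm. Visits are booked in advance, non-attenders are re-invited, and missing data are to be reported openly ({18b}, {20c}). Sensitivity analyses are commonly left to an analysis plan, which is not at hand. Adding self-reported re-treatment to the primary end-point would also bring back the re-intervention definition that {12} rejects as open to physician influence.

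Most of this stands, and it rules out three stronger readings that a reader might infer:

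- **That two hidden vsAR failures overturn the result.** With all men counted, they do so only if none of the 10 lost tAR men fails, and then by only 0.07 points on the Wald limit (-10.07%). If lost men in both arms fail at the planned rates, the chance of that combination is about 0.077 × 0.954¹⁰ = 0.077 × 0.624, or 5%.
- **That non-inferiority would be declared because failures left the trial.** The article gives no data on the direction of loss.
- **That the assumption is never tested.** An article without its analysis plan cannot show this.

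What remains is the stated rule. It censors a man even when the planned contact shows that he left because of a recurrence, and that contact is set up to record a reason only, not an outcome. An added analysis elsewhere would not change either of these.

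**Conclusion.** The point holds as a question of robustness. The stated censoring rule makes the primary comparison depend on loss being unrelated to failure, and at the plan's own figures the conclusion turns on few unseen outcomes. From 2 v 2 observed failures, three hidden failures among the 10 lost vsAR men remove non-inferiority when lost tAR men fail at the observed 5%; two are enough only if no lost tAR man fails, and one is not enough.

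These counts assume exactly 20% loss in each arm, 2 observed failures in each arm, and Wald or Newcombe limits as stand-ins for the Kaplan-Meier limit. They shift with the starting counts. From 1 v 1 observed failures, two hidden vsAR failures with no tAR failure among the lost give -9.0% (Wald) and -10.02% (Newcombe). The bias is possible, not shown. The trial remains valid, but its main claim needs this check.

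**What to change.** Keep the cystoscopic definition of failure and the planned censoring for the primary analysis. Make three additions:

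1. At the drop-out contact already planned in {20c}, record in structured form whether and when the man had a stricture recurrence or urethral treatment elsewhere. Ask the same questions in both arms.
2. Pre-specify a sensitivity analysis that counts such reports as failures at their date, in both arms alike.
3. Pre-specify a tipping-point analysis. Impute a rising number of failures among censored vsAR men, with censored tAR men at the observed tAR rate, and report the number at which the lower 80% limit passes -10%. Qualify the non-inferiority claim if that number is plausible.

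The cost is one or two questions in an existing contact, a short extra analysis, and possibly a more cautious conclusion. The tipping-point analysis needs no new data. Self-reported re-treatment is open to the physician influence described in {12}, which is why it stays out of the primary analysis.
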